# 5 TREATMENT OF SUBJECTS

## 5.1 Investigational treatment

#### Children of 8-9 years old will be asked to receive an extra pertussis-component in the DT-IPV booster vaccination (DT*Pacv*-IPV) together with their MMR vaccination. There will be no extra injection, only a change in vaccination composition (addition of the pertussis component). Pre- and post-vaccination a blood sample of 15 ml will be taken by venous puncture. Post-vaccination blood sampling will be done at 28 days (± 2 days) and 1 year (± 2 weeks) after the booster vaccination. To examine *B. pertussis* specific memory B- and T-cells we need a minimum of 1 x 106 Peripheral Blood Mononuclear Cells (PBMC's) to analyse one of the 5 most important *B. pertussis* specific antigens (Ptx, Prn, FHA, Fim 2 and 3). B- cells account for only 2 to 10% of all PBMC's and only 20-30% of all B- cells are memory B- cells. On average we can isolate 1 x 106 PBMC's per ml blood, however this is highly variable per person. To analyse specific memory B- cells to all 5 *B. pertussis* antigens, an amount of 15 ml blood is needed. With less material, B- cell responses against just one or two proteins of *B. pertussis* (Ptx, Prn or FHA) will be measured. In our ongoing study a blood sample of 15 ml is not a problem in 8-9 years old children.

##

## 5.2 Use of co-intervention (if applicable)

An extra ACV booster vaccination including a 3 components ACV combined by GSK (DTPacv-IPV, BoostrixTM) will be given together with their MMR vaccination that they receive according to the RVP.

**5.3 Escape medication (if applicable)**

Optionally, a local anaesthetic (Emla crème; AstraZeneca) will be used to minimize the pain of the venous puncture.

# INVESTIGATIONAL MEDICINAL PRODUCT

- Product: Boostrix Polio

Boostrix Polio is indicated for booster immunization against pertussis, diphteria, tetanus and polio as a single dose in individuals 4 years of age and older.

Each dose of 0,5 ml Boostrix Polio for intramuscular injection contains 2 IE Diphteria Toxin (Dtx), 20 IE Tetanus toxin (Ttx), 8 µg Ptx, 8 µg FHA, 2,5 µg Prn, 40 D-antigenunits IPV-1, 8 D-antigenunits IPV-2 and 32 D-antigenunits IPV-3 adsorbed onto 0,3 mg aluminimumphosphate.

### - How supplied Boostrix Polio is supplied in a glass vial with an elastic cap as provided by GSK.

# - Dosage and administration

Boostrix Polio must be at room temperature before administration. Before administration, shake vigorously to obtain a homogeneous, turbis, white suspension. Do not use if resuspension does not occur with vigorous shaking. Before injection, the skin at the injection site should be cleaned and prepared with suitable germicide.

Boostrix Polio should be administered as a single 0,5 ml injection by intramuscular route into the deltoid muscle of the upper arm.

- Storage

Boostrix Polio will be provided by GSK.

Boostrix Polio must be stored refrigerated between 2°C and 8°C. Boostrix Polio must not freeze and must be discarded if the vaccine has been frozen. Boostrix Polio must not be used after expiration date shown on the label. Damaged vials must be returned to GSK.

# METHODS

## 7.1 Study parameters/endpoints

#### 7.1.1 Main study parameter/endpoint

The main study parameters will be the longitudinal kinetics of B- and T- cell memory immune responses and antibody responses against the vaccine proteins of *B. pertussis*.

Blood samples will be separated in Peripheral Blood Mononuclear Cells (PBMC's) and plasma samples. PBMC's will be divided in purified B- cell populations and T- cell populations.

B- cells will be cultured and memory B- cells will be polyclonal stimulated (Bernasconi et al, 2002). After 5 days stimulation, B- cell memory responses will be measured against the various proteins of *B. pertussis* (FHA, pertactin, PT, Fim 2 and 3) by ELIspot assays and MIA (Multiplex Immuno Assay) or ELISA of the culture supernatants.

The plasma samples will be used to measure antibody responses against the various proteins of

*B. pertussis* (PT, PRN, FHA, Fim 2 and 3), and, if necessary to the extra components of the National Immunization Program. IgG and IgA antibody titer is measured in

multiplex immuno assay (MIA) (Gageldonk et al 2008) in two dilutions using FDA reference

serum as standard (EU/ml, Meade et al 1995).

## Randomisation, blinding and treatment allocation

No randomization or different treatment groups are designed in this study.

Personal data

Personal (identity) data are defined as the set of data that together might disclose the identity of a participant: name, date of birth, sex, and full address. The principal clinical investigator will guarantee that personal data from participants are treated anonymously, unless medical conditions of the participants require release of anonymity.

Study data

Study data are defined as the set of all participant-related variables such as: initials, postal code (only the four numbers), vaccination status, data on possible adverse events, antibody data. The storage of data is such that third parties have no access to the data.

- Data on the CRF

On the CRF the following data must be written:

- UTN (unique trial number)

- number of vial

- expiration date

- place of administration (left or right arm)

- name, date, signature of the person who have given the vaccination.

- remarks

## Study procedures

Since the most cases of *B. pertussis* infection occurs in 9 years old children nowadays, it is important to monitor the immune system of children in this age group. Study procedures will be done by qualified persons according to standard operating procedures.

The booster vaccination and blood samplings using venous puncture (15 ml) are performed by experienced physicians and study nurses. A local anesthetic (Emla crème) will be used to minimize the pain of the venous puncture. In case of resistance the behavior code of the Dutch Society of Pediatricians will be followed.

Parents will be asked to participate in the study by letter. When they fill in a reply-card, they will receive an informed consent by mail and will subsequently be contacted to make an appointment for their first visit in the pediatric outpatient’s clinic. During this visit, both parents will be asked to sign an informed consent after which the blood sampling will be done and the vaccination will be given. During the next visits at 28 days (± 2 days) and 1 year (± 2 weeks) after the vaccination, a venous blood sampling will be done. When the blood sampling will be difficult, the sampling will be stopped immediately.

Because we only need 20 children in the control group, we will recruit these children from the group of children who were not able to participate at the start of the Booster study, because we had too many registrations. We will contact the parents of these children again by phone. In addition we will send a newsletter (annex 1) to each participant of the Booster study to inform about the progress of the study and in which we also call up for children who could participate in the control group of the Booster study. When parents are interested in participation, we will sent the extra information (annex 2) about the study and the control group and we will make an appointment for blood sampling in the Spaarne hospital. During this visit, both parents will be asked to sign an informed consent for the control group (annex 3) after which blood sampling will be done. Data will be filled in the CRF for the control group (annex 4).

## Withdrawal of individual subjects

Parents of subjects can decide not to participate at any time for any reason without any consequences. The investigator can decide to withdraw a subject from the study for urgent medical reasons.

### Specific criteria for withdrawal (if applicable) not applicable

## Replacement of individual subjects after withdrawal

## Because we expect 15% of all children to prematurely withdraw from the study, we aim for 70 children at the start of the study, so there will be 60 children completing the study. For the control group we aim for 20 children.

## Follow-up of subjects withdrawn from treatment no follow-up

## Premature termination of the study

Because Boostrix-polio is a registered vaccine which is already used in other countries in the same age group (children 9-12 years of age), we don’t expect that serious side effects will occur. Therefore we don’t expect to premature terminate the study.

**8 SAFETY REPORTING**

**8.1 Vaccine information**

8.1 Study Product Accountability

Each time vaccines are used, a signed form with information on the quantity, expiration date and vial numbers of the delivered vaccines must be added. The form must be dated en signed by the person who is responsible for storage and the person who receives the product. The person who gives the vaccine is responsible for the accountability at the location.

If at the end of the study a discrepancy occurs between the number of delivered vaccines and the number of vaccine used, a written explanation must be obtained.

All unused vaccines will be returned to GSK at the end of the study.

8.2 Safety monitoring

# - Safety monitoring

Each child will be observed during 15 minutes after vaccination by the study nurse or doctor who gave the vaccination.

- Adverse events

Any untoward medical occurrence in a patient or clinical investigation subject administered a pharmaceutical product and which does not necessarily have a causal relationship with this treatment. An adverse event (AE) can therefore be any unfavourable and unintended sign (including an abnormal laboratory finding), symptom, or disease temporally associated with the use of a medicinal (investigational) product, whether or not related to the medicinal (investigational) product (see the ICH Guideline for Clinical Safety Data Management: Definitions and Standards for Expedited Reporting).

An serious adverse event is defined as each unexpected change in the medical situation, which

- causes death
- is live threatening
- causes admission to a hospital or which delays a current admission
- results in ongoing negative causes or handicaps

This classification will be used for the relation with the given vaccine

- Unlikely. There is no medical evidence suggesting the adverse event is related to the vaccination or another, more plausible explanation.
- Possible. There could be a possible medical explanation that the event is related to the vaccination. However, other medical explanations can not be excluded.
- Likely. There is a potent medical explanation for a causal relation between the administration of the vaccination and the adverse event. There are no possible other explanations for the adverse event.

Each SAE that occurs within a month after administration of the vaccine will be reported at the research centre and carefully registered and examined by the research group.

In case of a Suspected Unexpected Serious Adverse Reaction (SUSAR) that might be related to the administration of the vaccine, will be immediately reported to the vaccine distributor GSK and within 14 days to the CBG with a CIOMS form. The SUSAR will also be reported to the CCMO and the BI (Bevoegde Instantie).

The research doctors ([name] and [name]) can evaluate whether a SAE is a SUSAR.

- Adverse reactions Boostrix Polio

In clinical trials in which Boostrix Polio had been administered to adolescents and adults, most common adverse events within 24 hours after administering are:

very often >10%: pain, erythema and swollen site of the injection, fever (T>37,5C), fatigue

often 1-10%: fever (T>39,0C) in 4-8 year old children, erythema and swollen site of the injection,

malaise

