# - Documentation SAE and SUSAR

All adverse events or complications as been noticed by the parents, caregivers or research nurse or doctor must be written in the CRF.

Serious adverse events need to be reported on the SAE form as well.

The following criteria the adverse events will be used:

| Local reactions | Intensity | size of local reaction |
| --- | --- | --- |
| Redness and swollen | Mild | < 10 mm |
|  | Moderate | 10-29 mm |
|  | Severe | > 30 mm |

| Systemic reactions |  |  |
| --- | --- | --- |
| fever | 1 | 37,5-38,4 C |
|  | 2 | 38,5-39,4 C |
|  | 3 | 39,5-40,4 C |
|  | 4 | 40,5 C |
| Persistent, prolonged crying | Mild | 1 hour |
|  | Moderate | 1-3 hours |
|  | Severe | 3 hours |
| hyporesponsive episode | Severe | 3 hours |
| less active | yes/no |  |
| recuced apitite | yes/no |  |
| vomiting | yes/no |  |
| Diarhoea | yes/no |  |

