## Annual progress report

The sponsor/investigator will submit a summary of the progress of the trial to the accredited METC once a year. Information will be provided on the date of inclusion of the first subject, numbers of subjects included and numbers of subjects that have completed the trial, serious adverse events/ serious adverse reactions, other problems, and amendments.

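### Section 8.2 makes unexpectedness a condition of being an SAE, which fits neither the adverse-event definition beside it nor the later SUSAR step

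*Protocol*

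**What the plan says.** Section 8.2 sets out three layers of event.

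- **Adverse event:** "Any untoward medical occurrence in a patient or clinical investigation subject administered a pharmaceutical product", whether or not it is causally related. Expectedness is not mentioned.
- **Serious adverse event:** "An serious adverse event is defined as each unexpected change in the medical situation, which" has one of four outcomes: death, threat to life, a new hospital admission or delay of one already under way, or lasting harm.
- **SUSAR:** the term is spelled out ("In case of a Suspected Unexpected Serious Adverse Reaction (SUSAR) that might be related to the administration of the vaccine") but not otherwise defined. The research doctors "can evaluate whether a SAE is a SUSAR".

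Three actions depend on the SAE label:

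- Section 8.2: "Each SAE that occurs within a month after administration of the vaccine will be reported at the research centre", followed by registration and examination by the research group.
- Section 8.2, Documentation SAE and SUSAR: "Serious adverse events need to be reported on the SAE form as well".
- Section 11.3: the yearly summary to the ethics committee covers, among other items, "serious adverse events/ serious adverse reactions, other problems, and amendments".

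One rule does not depend on the label: "All adverse events or complications as been noticed by the parents, caregivers or research nurse or doctor must be written in the CRF".

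**The concern.** An SAE is normally an adverse event with a serious outcome, and expectedness is judged afterwards, when deciding whether a suspected reaction needs expedited reporting. Here expectedness enters one step early. An adverse event that puts a child in hospital could fail to be an SAE only because it was foreseeable. The participants are healthy children, and the SAE label opens the way to the research group's review and the SAE form. At stake is how completely serious events are labelled and reviewed. The estimates of immune response are not involved.

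**Working it through.** The point concerns a definition and the plan gives no figure to reproduce, so the check sets the passages side by side.

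**Step 1. Apply Section 8.2 literally.** Take an adverse event that meets one of the four outcomes, and assume that *unexpected* means the same in the SAE definition as in the term SUSAR.

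| Serious outcome and | In CRF as AE | SAE as written | SUSAR | SAE after the fix |
|---|---|---|---|---|
| unexpected, relation suspected | yes | yes | yes | yes |
| unexpected, relation not suspected | yes | yes | no | yes |
| expected, relation suspected | yes | **no** | no | yes |
| expected, relation not suspected | yes | **no** | no | yes |

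Three things follow. Every row reaches the CRF. The last two rows lose the SAE report, the SAE form and the SAE count. The set of SUSARs is the same before and after the fix, so expedited reporting is not affected.

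**Step 2. Look at the SUSAR step.** If every SAE is already unexpected, the only thing that separates a SUSAR from other SAEs is suspected relation to the vaccine. The word *unexpected* in SUSAR then does no work. It has a function only if SAEs can also be expected, which the SAE definition rules out. This is the inconsistency.

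**Step 3. Look for a correction elsewhere.** No other section restates the SAE definition without the condition. Section 10.1 says the CCMO and the competent authority will be told of events that are severe or unexpected and may affect participant safety. It treats the two properties as alternatives. That gives a second reporting route, but for severe events, which is not the same term as serious. Section 11.3 also asks for other problems, which gives a third.

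**Step 4. Size.** The list of vaccine reactions in Section 8.2 contains pain, redness, swelling, fever, fatigue and malaise. None is serious in itself. The most plausible candidate is fever above 39.0 °C, listed at 1–10% in children aged 4–8, a range that overlaps the study's 8–9 years. If that range applied to all 70 vaccinated children:

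- 70 × 0.01 = 0.7 children
- 70 × 0.10 = 7 children

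That is the number with the fever. Only those who were also admitted, and whose event was then classed as expected, would fall outside the SAE definition. The protocol gives no admission proportion, so the affected number is an unknown fraction of 0.7 to 7 for this reaction. Section 7.7 expects no serious side effects.

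**The case against.** The strongest reply is that *unexpected* was loose English for untoward or unplanned. It qualifies a change in the child's medical situation, whereas in SUSAR it qualifies a reaction. On that reading, admission of a healthy child after a booster is an unexpected change even when fever is a listed reaction, and nothing is excluded. The rest of the list is also loosely worded. This reading is plausible, but the text does not state it, and staff have only the written definition to apply.

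A reader might also infer more than the documents support:

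- **That the SAE wording contradicts the adverse-event and SUSAR definitions.** SAEs are a subset of adverse events, so a narrower subset is not a logical contradiction. SUSAR is only spelled out. Research doctors sorting SUSARs from SAEs is still possible on relatedness alone. The fault is inconsistency.
- **That SAE counts are understated by rule.** This needs expected serious events to exist. The listed reactions are not serious in themselves, and the plan shows no such case.
- **That such events are missing from the safety record or the annual report.** The CRF takes all noticed adverse events, and Sections 10.1 and 11.3 leave other routes. What is lost is the SAE label and the actions tied to it.
- **That someone is assigned to judge expectedness before reporting.** The protocol assigns this to no one. It is only a consequence of the literal wording.

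**Conclusion.** The point holds as an inconsistency in a definition, and it is minor. Section 8.2 makes unexpectedness a condition of being an SAE, no other section corrects this, and the same property is used again at the SUSAR step. Read literally, an expected serious event stays in the CRF as an adverse event without SAE-level reporting.

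Few such events, if any, are likely among about 70 vaccinated children. Safety is neither an objective (Section 2) nor a main study parameter (Section 7.1.1), and Section 9 plans no analysis of SAE rates, so no efficacy conclusion changes. The verdict assumes that *unexpected* is read in its usual safety-reporting sense. If it was meant as untoward, no event is excluded and only the wording needs repair.

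**What to change.** In Section 8.2, delete *unexpected* from the SAE sentence. Define an SAE as any adverse event, as defined in the preceding paragraph, that meets one of the listed outcomes, regardless of expectedness. Apply unexpectedness only when judging whether an SAE is a SUSAR. Because the new sentence rests on the adverse-event definition, an occurrence that is not untoward stays outside it.

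Check that the SAE form agrees. It is not among the documents at hand and may or may not repeat the present wording.

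The cost is one sentence, a possible matching change to the form, and possibly a few more SAE forms.

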# - Documentation SAE and SUSAR

All adverse events or complications as been noticed by the parents, caregivers or research nurse or doctor must be written in the CRF.

Serious adverse events need to be reported on the SAE form as well.

The following criteria the adverse events will be used:

| Local reactions | Intensity | size of local reaction |
| --- | --- | --- |
| Redness and swollen | Mild | < 10 mm |
|  | Moderate | 10-29 mm |
|  | Severe | > 30 mm |

| Systemic reactions |  |  |
| --- | --- | --- |
| fever | 1 | 37,5-38,4 C |
|  | 2 | 38,5-39,4 C |
|  | 3 | 39,5-40,4 C |
|  | 4 | 40,5 C |
| Persistent, prolonged crying | Mild | 1 hour |
|  | Moderate | 1-3 hours |
|  | Severe | 3 hours |
| hyporesponsive episode | Severe | 3 hours |
| less active | yes/no |  |
| recuced apitite | yes/no |  |
| vomiting | yes/no |  |
| Diarhoea | yes/no |  |

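### The adverse-event criteria do not match the reactions that the protocol expects: no item for injection-site pain, at most a yes/no proxy for fatigue and malaise, and no grade at exactly 30 mm

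*Protocol*

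**What the plan says.** All the relevant text is in section 8.2 of the Protocol.

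**Expected reactions.** The part on adverse reactions to Boostrix Polio gives frequencies for events within 24 hours, from trials described as being in adolescents and adults. The most frequent group reads "very often >10%: pain, erythema and swollen site of the injection, fever (T>37,5C), fatigue". The next reads "often 1-10%: fever (T>39,0C) in 4-8 year old children, erythema and swollen site of the injection", and malaise completes that list.

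**Recording.** The part on documentation of SAEs and SUSARs first requires every adverse event noticed by parents, caregivers or study staff to be entered in the CRF. It then introduces its tables with "The following criteria the adverse events will be used".

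- The local table has one entry, graded by size: "Redness and swollen | Mild | < 10 mm", then "Moderate | 10-29 mm", then severe for anything above 30 mm.
- The systemic table has seven items. Fever has four grades, the first being "fever | 1 | 37,5-38,4 C". Crying is graded by duration and a hyporesponsive episode is classed as severe. Being less active, reduced appetite, vomiting and diarrhoea are yes/no.

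**The concern.** The two parts of section 8.2 should fit together, because a recording table for a known vaccine ought at least to cover the reactions that the same section says are common. Here the first-named reaction in the most frequent group has no item, and two others have no intensity scale.

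What is at stake is the description of reactogenicity. Section 5.1 says that the children receive no additional injection, only an added pertussis component. Reactions to that component are therefore, besides blood sampling, the main burden that the study adds for healthy children.

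Unsolicited reporting is a weak substitute for a set question. Children are observed for 15 minutes, the listed reactions fall within 24 hours, and the next visit described in section 7.3 is at 28 days. The 30 mm gap is smaller, but it falls on a natural rounding point and leaves the grade to whoever fills in the form.

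**Working it through.** The plan states no figure to reproduce here. The check sets the list of expected reactions against the table and then sizes the gap.

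**1. Item-by-item comparison (both parts of section 8.2)**

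| Expected reaction | Listed frequency | Item in the criteria | Intensity grade |
| --- | --- | --- | --- |
| Injection-site pain | >10% | none | no |
| Erythema | >10% | redness, by size | yes |
| Swelling | >10% | swelling, by size | yes |
| Fever above 37.5 C | >10% | fever, four grades | yes |
| Fatigue | >10% | nearest is less active | no, yes/no only |
| Malaise | 1-10% | nearest is less active | no, yes/no only |

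Of the five reactions listed above 10%, three have an intensity scale, one has at most a yes/no proxy and one has no item.

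**2. Coverage of the size bands**

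The bands are below 10 mm, 10 to 29 mm, and above 30 mm. Running every whole millimetre from 0 to 100 through them leaves exactly one value without a grade: 30. With finer measurement, anything above 29 mm and up to and including 30 mm is also ungraded.

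**3. How many children this touches**

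Inputs: 70 children to be vaccinated (section 4.4) and a 10% lower bound for pain (section 8.2). Using that bound at 8-9 years is an assumption, because the source trials are described as being in adolescents and adults.

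- Expected number with pain, at least: 70 × 0.10 = 7.
- Chance of at least one case: 1 − 0.9^70 = 0.999.
- The expected count is proportional to the rate: half of it, 5%, would give 70 × 0.05 = 3.5.
- Fatigue is in the same group, so the same bound of 7 applies.
- Malaise at 1-10%: 70 × 0.01 = 0.7 to 70 × 0.10 = 7 children.

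These counts show only that the ungraded reactions will almost certainly occur. They say nothing about how severe they will be.

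**The case against.** The strongest reply is that little is lost. Reactogenicity is neither an objective (section 2) nor a main study parameter (section 7.1.1), and section 9 plans no safety analysis. Section 7.7 describes the vaccine as registered and already used at 9-12 years. The controls give one blood sample a year after their regular DTP vaccination, so graded pain could not be compared between the groups anyway. All of this stands, and it limits the weight of the point.

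Three stronger readings might be inferred, and the documents do not support them.

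- **That the reactions expected most cannot be graded.** Erythema, swelling and fever are all in the group above 10% and all have grades. Malaise is in the 1-10% group.
- **That the criteria are an infant scale.** Items such as "Persistent, prolonged crying" do suggest younger children, but at most two of the seven systemic items are of that kind; the other five fit any age. The hyporesponsive item also has a basis in this protocol, because section 4.3 names such episodes after an earlier vaccine as a reason not to give Boostrix Polio.
- **That pain would go unrecorded.** The general rule requires noticed events to be entered, so noticed pain can be counted. What is missing is a set question and a defined intensity. The CRF is an annex and is not shown; it may hold a pain field. If it does, section 8.2 should say so.

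On 30 mm, comparison signs seem to be missing from other cells in the available text, such as the top fever grade and the crying rows. Those cells are not counted as errors. The sign before 30 mm is present, so the gap is read as real, but it is worth a look at the original table.

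**Conclusion.** The point holds in limited form. The criteria in section 8.2 do not match the reactions that the same section expects: injection-site pain has no item, fatigue and malaise have at most a yes/no proxy, and exactly 30 mm has no grade. This is not a detail left for a later analysis plan, because the protocol fixes the criteria itself.

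Pain is expected in at least 7 of 70 vaccinated children if the 10% lower bound carries over to 8-9 years. Noticed cases would reach the CRF without a solicited question or a predefined grade, unless the CRF annex already supplies them.

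The consequence is minor. Reactogenicity data would be incomplete and less uniform, while the conclusions on memory B- and T-cell and antibody responses would not change. The correction is cheap enough to be worth making.

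**What to change.** Reconcile the table in section 8.2 with the list of expected reactions in the same section:

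1. Add injection-site pain, and fatigue/malaise, each with a defined intensity grade.
2. Make the size bands for redness and swelling contiguous, so that 30 mm has one grade. Which band it joins is for the sponsor to decide.
3. Ask every vaccinated child about these items in the same way, so that the counts do not depend on who happens to volunteer a complaint.
4. Keep the existing items, including the hyporesponsive episode.

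The cost is one revised table and a slightly longer CRF page. If the questions are asked only at the 28-day visit, answers rest on about four weeks' recall of reactions listed within 24 hours. The protocol should acknowledge that, or collect the answers closer to vaccination at some extra burden to families.
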